#### Skeletal muscle biopsy

A portion of the muscle sample (~ 75 mg) is cleaned of residual blood, fat, and connective tissue and subsequently flash frozen. About 50 mg is used for myoblast isolation (described below), and approximately ~ 25 mg is immediately fixed in zinc-buffered formalin. Primary myoblasts are isolated from the muscle biopsies as previously described [33]. Briefly, muscle tissue is minced, and trypsin digested (0.25% trypsin EDTA diluted 1:4 in Ham’s F-12). Digested muscle tissue is plated in growth media [Ham’s F-12 nutrient mixture with 10% fetal bovine serum, 2% l-glutamine, and 2.5 ng/ml recombinant human fibroblast growth factor (R&D systems, Minneapolis, MN)] to allow fibroblasts to adhere to the plate. Supernatant containing muscle tissue and myoblasts is transferred to a fresh plate and myoblast colonies are allowed to grow for 1 week. Thereafter, media is changed every other day and passaged at 80–90% confluence and cryopreserved after each passage. Experiments are performed with myoblasts at passage (P)3 or P4.

#### Mitochondrial function

Mitochondrial oxygen consumption rate (OCR) is measured using a Mito Stress Test and Seahorse XFe96 technology (Agilent Technologies, Santa Clara, CA) as previously published [33]. Briefly, myoblasts are seeded in triplicate on a collagen-coated 96-well Seahorse plate (35,000 cells/well) and maintained under standard cell culture conditions. After 24 h, growth media is replaced with XF Assay Medium (pH 7.4) with sodium pyruvate (1 mM), l-glutamine (2 mM), and glucose (10 mM) and incubated at 37 °C without CO_2_ for 1 h before measuring myoblast OCR. Respiratory parameters are assessed by the sequential addition of oligomycin (1.5 µM), carbonyl cyanide‐p‐trifluoromethoxyphenylhydrazone (FCCP; 2 μM), and rotenone/antimycin A (0.5 μM). Resulting OCR measurements are normalized to cell count obtained by staining nuclei with Hoechst dye (2 µM; ThermoFisher Scientific, Waltham, MA) and visualizing on a BioTek Cytation 1 cell imaging multi-mode reader (BioTek, Winooski, VT).

#### Glycolytic function

To quantify glycolytic function, capacity, and reserve, a Glycolysis Stress Test is performed using Seahorse XFe96 technology. Myoblasts are plated in Seahorse plates with glucose- and pyruvate-free XF Assay Medium (pH 7.4) with L-glutamine (2 mM). Myoblasts are incubated at 37 °C without CO_2_ for 1 h before measuring myoblast extracellular acidification rate (ECAR) at baseline and after the sequential addition of glucose (10 mM), oligomycin (1.5 uM), and 2-deoxyglucose (2-DG; 50 mM). Measures are normalized to cell count as described above.

#### Mitochondrial volume

Myoblasts are incubated with growth media containing MitoTracker Deep Red FM (Invitrogen, Carlsbad, CA) (100 nM) under standard cell culture conditions for 30 min as previously published [33]. Cells are prepared for flow cytometry using the PerFix-nc Kit (Beckman Coulter, Brea, CA). Ten-thousand events per sample are acquired and excited by a 633 nm wavelength laser line using flow cytometry (BD FACSCanto II, Becton, Dickinson and Company, Franklin Lakes, NJ). Fluorescence is analyzed using FlowJo software (version 10.7.1, Becton, Dickinson, and Company) and the mean fluorescence intensity (MFI) of each experimental sample determined.

#### RNA and DNA isolation and quantitative real-time polymerase chain reaction (qPCR)

To assess expression of genes, and microRNAs, total RNA is extracted from flash frozen SKM samples (~ 10 mg) using the miRNeasy Mini Kit (Qiagen, Valencia, CA) and cDNA synthesized using the QuantiTect reverse transcription kit (Qiagen) [33]. Custom primers designed to span exon-exon junctions are purchased from Integrated DNA Technologies (Coralville, IA). qPCR reactions are carried out in duplicate using a CFX96 thermal cycler (Bio-Rad, Hercules, CA) with ribosomal protein S13 (*RPS13*) as the endogenous control. Data is analyzed using the 2^−ΔΔCt^ method.

#### Plasma microRNA expression

To assess the expression of circulating microRNAs, total RNA is extracted from 200 μL of fasting plasma using the miRNeasy serum/plasma kit (Qiagen) as previously described [34]. For normalization, 25 fmol of synthetic miR-cel-238 is added to each RNA sample. cDNA is synthesized using the Reverse transcription kit (Thermofisher) and mature miRs measured using TaqMan primers and Universal PCR Master Mix II (ThermoFisher, Waltham, MA). Serial dilutions of known concentrations of miRs (Integrated DNA Technologies, Coralville, Iowa) of interest are used to generate standard curves and miR expression represented as copy number per μL and normalized to copies of miR-cel-238.

#### Secondary outcomes

Changes in alcohol use are assessed using TLFB and Peth pre- and post-exercise intervention. Healthy Eating index (HEI) using Automated Self-Administered 24-h Dietary Assessment Tool (ASA24); Montreal Cognitive Assessment (MoCA); Hospital Anxiety and Depression Scale (HADS); and 36-Item Short Form Health Survey (SF-36) scores; pre and post exercise intervention are used to assess changes in dietary patterns, cognitive ability, and overall quality of life. The ASA24 is based upon the United States Department of Agriculture's (USDA) Automated Multiple-Pass Method (AMPM). Data from multiple validation and evaluation studies indicate good to strong agreement between the ASA24 system and standardized interviewer-administered 24-h recalls. Furthermore, data are well estimated for HEI scores based on the 24-h dietary recall [35]. The reliability of MoCA is 0.89, and the intraclass correlation coefficient of 0.955 and is shown to be good. Additionally, with a cut-off of 26 points, a sensitivity of 80% and specificity of 75% is reported [36]. The HADS has been found to perform well in assessing the symptom severity and presence of anxiety disorders and depression symptoms in both somatic, psychiatric, and primary care patients and in the general population [37]. Finally, the SF-36 was developed as a set of generic, coherent, and easily administered quality-of-life (QOL) measures. These measures rely upon participant self-reporting, provide a direct quantitative indication of an individual's health status, and is widely used as a QOL evaluation tool [38, 39].

### Data management and analysis

All data are entered into REDCap and are handled with confidentiality. Personal information of participants such as phone number and email addresses are used only to contact the participant. Names of participants appear only in the demographic form. The participants’ demographic and outcome measures of interest pre- and post-exercise intervention will be summarized using descriptive statistics. Mean, standard deviation, and range will be calculated for continuous variables, and frequencies and percentages will be generated for categorical variables. For continuous variables (such as VO_2max_, OCR, ECAR), the normal distribution assumptions will be tested. If necessary, the data will be transformed to follow the normal distribution assumption. If the normality assumption cannot be met, these variables will be classified as categorical or analyzed using non-parametric tests. For categorical variables (e.g., glucose at 2 h, HOMA-IR, HOMA-b) clinical cutoff values will also be used. The changes in the outcome measures (e.g., OGTT outcomes, bioenergetic measures, microRNA expression, RHR, VO_2max_, MOCA measures, ASA24 measures) between pre and post exercise intervention will be tested using the paired t-test. Linear regression models will also be used to analyze the relationship between alcohol use with the outcome measure changes as the dependent variable, adjusting for potential confounding factors (such as age, sex, race, viral load and CD4 counts). If there is matching or balance achieved, age and gender will be used as categorical variables rather than confounders. A p < 0.05 will be used for statistical significance.

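### Outcomes that stay non-normal after transformation may be cut into categories instead of ranked, with no rule for choosing; 2-h glucose and HOMA are mislabelled categorical

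*Protocol article*

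**What the plan says.** All of the relevant text is in the protocol article, section Data management and analysis. It sets out a sequence:

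1. A check: "For continuous variables (such as VO_2max_, OCR, ECAR), the normal distribution assumptions will be tested".
2. A first remedy: "If necessary, the data will be transformed to follow the normal distribution assumption".
3. A second remedy if that fails: "If the normality assumption cannot be met, these variables will be classified as categorical or analyzed using non-parametric tests".

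The next sentence turns to the glycemic measures: "For categorical variables (e.g., glucose at 2 h, HOMA-IR, HOMA-b) clinical cutoff values will also be used". The one after it gives the main test. Changes in a list of outcomes that opens with OGTT outcomes, bioenergetic measures and microRNA expression "between pre and post exercise intervention will be tested using the paired t-test". Linear regression then takes the outcome changes as the dependent variable. The significance rule is "A p < 0.05 will be used for statistical significance".

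The OGTT part of Outcome measures describes plasma glucose read on an analyzer at 0, 1 and 2 h, and HOMA-IR and HOMA-β calculated by formula from fasting glucose and insulin. All three are therefore continuous quantities.

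**The concern.** There are two separate faults.

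**The fallback.** Step 3 offers two very different methods and no rule for choosing between them, for which outcome, or at what cut-point. A failed normality assumption is no reason to categorise. The rank test named in the same sentence needs no normality and keeps almost all the information. Categorising discards every change that does not cross the cutoff. With a few dozen pairs, a real improvement in an outcome such as OCR or ECAR could be reported as null. The choice would also be made with the data in view.

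**The label.** Calling 2-h glucose, HOMA-IR and HOMA-β categorical conflicts with how they are obtained, and with the paired t-test and linear regression that the same paragraph applies to outcome changes. The abstract places whole-body glucose-insulin dynamics in the primary outcome, so the scale of these measures should not be in doubt.

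A smaller point is that the check is described for the variables, whereas the paired t-test needs approximate normality of the within-person differences.

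**Working it through.** The article states no sample size, power, effect size, SD or pre-post correlation, so there is no figure of its own to reproduce. The question is what the categorical branch would cost if it were used.

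**Inputs from the article**
- Significance level 0.05 (taken as two-sided; the article does not say).
- Main test: paired t-test.
- 33 participants with all post-intervention measures as of November 2022 (Results). This is an interim count, not a planned size.
- 63 pre-intervention biopsies (Results), used as an upper bound for pairs.

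**Assumptions**
- Standardised paired change dz = 0.5, also 0.8.
- Pre-post correlation ρ = 0.5, 0.7 or 0.8.
- 50%, 30% or 15% of participants above the cutoff at baseline, giving nine settings.
- Bivariate normal data; categorised outcomes compared by McNemar's test. The article names no test for categories.

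**Continuous analysis, n = 33, dz = 0.5.** The noncentrality is dz·√n = 0.5 × √33 = 2.87, the critical value t(0.975; 32) = 2.04, and power is 79.5%. The change giving exactly 80% power is dz = 0.503. Simulated Wilcoxon signed-rank power is 78%.

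**After a fixed cutoff, n = 33, dz = 0.5.** With unit-variance pre and post values, the SD of the differences is √(2(1−ρ)) and the mean shift is dz times that. For ρ = 0.7: SD = √0.6 = 0.775, shift = 0.387. With the cutoff at the baseline median, the probability of crossing in the direction of improvement is 0.213 and in the other direction 0.062. McNemar's test therefore rests on about 33 × 0.213 = 7.0 against 33 × 0.062 = 2.1 participants; the other 24 or so contribute nothing. Power is 26% (exact) or 36% (mid-p).

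| ρ | Above cutoff at baseline | Exact McNemar | Mid-p |
|---|---|---|---|
| 0.5 | 50% | 35% | 45% |
| 0.5 | 30% | 24% | 34% |
| 0.5 | 15% | 9% | 17% |
| 0.7 | 50% | 26% | 36% |
| 0.7 | 30% | 18% | 27% |
| 0.7 | 15% | 5% | 12% |
| 0.8 | 50% | 19% | 28% |
| 0.8 | 30% | 12% | 21% |
| 0.8 | 15% | 3% | 8% |

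Against 80%, more than half the power is lost in 9 of 9 settings with the exact test and in 8 of 9 with mid-p. The exception loses (80 − 45)/80 = 44%.

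**Where the loss is smaller**

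| Pairs | dz | Paired t | Exact McNemar, nine settings | Loss under half in |
|---|---|---|---|---|
| 33 | 0.8 | 99% | 8–75% | 3 of 9 |
| 63 | 0.5 | 97% | 17–68% | 3 of 9 |
| 63 | 0.8 | about 100% | 41–97% | most |

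If categorising meant only classing each person as improved or worsened (a sign test), power at n = 33 and dz = 0.5 is about 56%, a loss of (80 − 56)/80 = 30%.

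**Type I error from the open choice.** Simulation with no effect, n = 33, ρ = 0.7, median cutoff and a Shapiro-Wilk pretest at 0.05: taking the smaller p-value of Wilcoxon and exact McNemar after a failed pretest gives about 5.5–6.0%. Taking the smallest of all three tests gives about 7.4–8.0%, but the plan does not propose that.

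**Scale of the glycemic measures.** Side by side, Outcome measures obtains them as continuous values; one sentence of the analysis section calls them categorical and adds clinical cutoffs with the word *also*; the next sentence tests OGTT outcomes by paired t-test. The label contradicts the other two, but nothing removes the continuous analysis.

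**The case against.** The strongest reply is that categorising is a last resort. Transformation comes first, and skewed measures such as HOMA-IR or microRNA copy number may well be acceptable on a log scale. Even then a rank test is available, so the power loss may never arise. That is right, and it makes the loss conditional. It does not justify keeping the categorical branch: when transformation has failed, the rank test is still the better choice.

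A reader might infer that the primary glycemic outcomes will be analysed only as categories and so lose most of their power. The text does not support this. Cutoffs are used in addition, OGTT outcomes stay under the paired t-test, and the examples given for the categorise-or-rank fallback are VO2max, OCR and ECAR. For the glycemic measures only the contradictory label stands.

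A reader might also infer that the open choice seriously inflates false positives. For a single outcome, the simulated rise to 5.5–6.0% is modest.

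On the normality check, the article says that "the normal distribution assumptions will be tested" without excluding change scores. It is fair to ask for clarity, but not to say that the wrong quantity will certainly be tested.

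Finally, a condensed article may leave detail to an analysis plan. That excuses silence on which outcomes get a log scale. It does not excuse the categorical option, which the article itself states.

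**Conclusion.** The point holds in a limited form. The plan states an inferior fallback, categorisation, beside a better one and gives no rule for choosing. If it is used with 33 pairs, dz = 0.5 and a fixed cutoff, power drops from about 80% (paired t) or 78% (signed-rank) to 3–35% (exact McNemar) or 8–45% (mid-p). These figures rest on an interim count and on assumed effect, correlation, cutoff and test. A loss of more than half is typical under those conditions but is not a general result. The false-positive cost of the open choice is small. The categorical label on 2-h glucose, HOMA-IR and HOMA-β contradicts the rest of the article and needs correcting, but it discards no power by itself. The change should be made before the final analysis.

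**What to change.** In Data management and analysis:

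- Delete the option to classify non-normal variables as categorical. Make the Wilcoxon signed-rank test on the paired differences the only fallback once transformation has failed.
- State that normality is checked on the within-person differences.
- Describe 2-h glucose, HOMA-IR and HOMA-β as continuous, with the continuous analysis as the main one.
- Label the clinical-cutoff analyses as supportive.

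The cost is analysis wording only: no new data, visits or participants. The article reports phase 2 as ongoing at submission, so the wording can be settled before the final analysis.

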## Results

The first phase of the study that determined whether PLWH with at-risk alcohol use had increased risk of dysglycemia and dysregulated muscle metabolic function are published.Results indicate that in response to an oral glucose tolerance test (OGTT) in PLWH with fasting dysglycemia; participants with at-risk alcohol use were five times more likely to meet criteria for prediabetes/diabetes. At-risk alcohol use was negatively associated with fasting C-peptide levels, increased odds of decreased HOMA-β, and increased 2-h glucose values [32]. These changes in whole body glucose insulin dynamics were also associated with skeletal muscle mitochondrial bioenergetic dysfunction.Bioenergetic health index (BHI), a positive indicator of mitochondrial bioenergetic health, was lower, and non-mitochondrial oxygen consumption was higher with increasing AUDIT scores. Proton leak, indicating decreased ATP synthesis, was significantly associated with higher 2-h glucose levels and AUDIT score, and myoblast mitochondrial volume was positively associated with the interaction between 2 h glucose and AUDIT. In addition, expression of genes associated with lipid handling were significantly decreased with the interaction of 2-h glucose and AUDIT, and expression of genes controlling mitochondrial biogenesis and dynamics were significantly decreased with higher 2-h glucose levels and AUDIT scores, respectively [33]. All these findings indicate that skeletal muscle mitochondrial health and bioenergetic function are dysregulated with at-risk alcohol use and dysglycemia.We were also able to demonstrate that recent alcohol use (PEth) influenced associations between circulating microRNAs implicated in metabolic function. Expression of miR-206 (muscle enriched) was significantly lower, and expression of miR-let-7b and miR-146a (adipose enriched) were significantly higher in PLWH with positive PEth. Participants with no recent alcohol use had miR-133a (muscle enriched) and miR-221 (adipose enriched) expression levels associated with altered glucose/insulin dynamics. While in participants with positive PEth, miR-20a (liver enriched) and miR-375 (pancreas enriched) together strongly predicted increased 2 h glucose levels [34]. Thus, results indicate that associations between circulating miRs and measures of glucose/insulin dynamics are modulated by alcohol use suggesting unique pathophysiological mechanisms contributing to altered glucose homeostasis in PLWH.

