At the time of submission of the manuscript, the second phase of the study is ongoing. Based on prescreening, or preliminary eligibility from the parent NOAH study, 395 PLWH were assigned an ALIVE-Ex specific ID, out of whom 318 came for consent visits. Of the 242 consented, 155 met eligibility criteria. The general demographics of the participants enrolled are shown in Table 2. One hundred and fifty-two (152) participants underwent pre-exercise OGTT and of these, 84 subjects underwent medical clearance. Sixteen subjects did not fulfill eligibility criteria as shown in Table 3. Sixty-three pre-muscle biopsies were performed and as of November 2022, 33 participants have completed exercise, post intervention fitness assessments, OGTTs and muscle biopsies.

**Table 2 Tab2:** Demographic Parameters of the ALIVE-Ex Study

Demographics	(n = 155)
	% (n)
Sex	
Female	31.6(49)
Male	69 (107)
Race	
African American	76.8 (119)
White	20.6 (32)
Other	1.9 (3)
Age, years	
20 to 30	6.4 (10)
31 to 40	14.2 (22)
41 to 50	18 (28)
51 to 60	45.8 (71)
60 +	15.4 (24)
Income	
< $20,000	84.5 (131)
$20,000 to $39,999	9 (14)
$40,000 +	6.4 (10)
Education	
< High School	34.8 (54)
High School Graduate	28.3 (44)
Some College, Junior/Community College, Vocational/Trade School	26.4 (41)
4-year College/Graduate/Professional School	10.3 (16)

**Table 3 Tab3:** Reasons for being ineligible for exercise of the ALIVE-Ex Study

Reason for ineligibility	Number
Active cocaine or amphetamine use	9
Angina	1
Lidocaine allergy	1
Uncontrolled hypertension	3
Orthopedic complications	2
Total	16

We anticipate that the exercise intervention will result in an increase in cardiorespiratory fitness reflected as decreased Resting Heart Rate (RHR) and increased VO_2max_. We also anticipate that the exercise intervention will improve OGTT outcome measures. We predict that the exercise will positively impact muscle bioenergetic measures and this will associate with overall changes in glycemic measures. We anticipate that exercise will have the greatest impact on these outcome measures in people with at-risk alcohol use. Although the intervention’s objective was not to improve other lifestyle choices such as diet and alcohol use, the analysis will identify whether exercise changes dietary patterns and alcohol use. It will also identify whether there is an improvement in cognitive measures and overall quality of life.

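### The rule that lets observed balance decide how age and gender enter the alcohol regression should go, and the alcohol coefficient should be shown with and without the outcome's baseline value

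*Protocol article*

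**What the plan says.** All of the analysis text is in the protocol article, Data management and analysis. Pre-post changes are tested with paired t-tests. A second analysis follows: "Linear regression models will also be used to analyze the relationship between alcohol use with the outcome measure changes as the dependent variable". Its covariates are introduced only by way of example, and the outcome's own baseline value is not in the list. The same section also sets a rule for two of those covariates: "If there is matching or balance achieved, age and gender will be used as categorical variables rather than confounders". No criterion for balance is stated. The threshold is "A p < 0.05 will be used for statistical significance". The wording that leaves the covariate list open is "adjusting for potential confounding factors (such as age, sex, race, viral load and CD4 counts".

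Two statements in Results bear on this model. Phase 1 reported that "At-risk alcohol use was negatively associated with fasting C-peptide levels, increased odds of decreased HOMA-β, and increased 2-h glucose values". For phase 2 the article says: "We anticipate that exercise will have the greatest impact on these outcome measures in people with at-risk alcohol use". As of November 2022, "33 participants have completed exercise, post intervention fitness assessments, OGTTs and muscle biopsies".

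**The concern.** There are two separate defects in one model.

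**Age and gender.** The balance sentence offers categorical coding as an alternative to treating a variable as a confounder. These are different questions: one is how a covariate is parameterised, the other is whether it is in the model and why. Because the choice waits on an observed and undefined balance, several models are open to the analyst once the data are in, each judged at the same 0.05 threshold.

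**Baseline value.** The exposure is associated with the starting level of the glycaemic outcomes, the dependent variable is change from that level, and the expected finding is more improvement in the group that starts worse. Regression to the mean produces the same pattern when part of the starting difference is temporary. If only the change-score coefficient is reported, a reader cannot separate a greater benefit of exercise from mean reversion.

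**Working it through.** The article gives no standard deviation, pre-post correlation, sample size or power for this analysis, so there is no figure to reproduce. The inputs marked as assumed are illustrative.

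**1. The age and gender rule**

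- *Is anything matched?* The article describes one exercise programme with testing before and after it. It describes no matched selection, and alcohol use is measured by AUDIT, TLFB and PEth, not allocated.
- *Does categorical coding replace adjustment?* No. Sex is already categorical, so for sex the sentence changes nothing unless it means leaving sex out. For age it either groups a continuous variable, which loses information and can leave residual confounding, or drops the adjustment.
- *How much imbalance could count as balance?* The article does not say. Suppose balance meant a non-significant two-sided 5% test, with 33 completers and the 57% at-risk share of the parent cohort (Background), giving about 19 and 14 people (both assumptions). The standard error of a standardised difference is √(1/14 + 1/19) = 0.352, and 1.96 × 0.352 = 0.69. Age gaps of up to about 0.69 SD would pass as balanced.

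**2. Bias from the baseline gap**

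Take an outcome where lower is better, such as 2-h glucose, with no true alcohol effect. A negative coefficient then means more apparent improvement in at-risk drinkers. For outcomes where higher is better, the signs reverse.

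- d = baseline gap, at-risk minus other, in SD (assumed 0.5; the documents give no size)
- r = pre-post correlation within alcohol group (assumed 0.4 to 0.8), with equal variances before and after
- f = share of the gap that is transient (unknown, 0 to 1)

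The pre gap is d and the post gap is (1 − f)d. Therefore:

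- change-score coefficient = (1 − f)d − d = −f·d
- baseline-adjusted coefficient = (1 − f)d − r·d = (1 − r − f)·d

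With d = 0.5:

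| Gap | Model | r = 0.4 | r = 0.6 | r = 0.8 |
|---|---|---|---|---|
| Stable, f = 0 | change score | 0 | 0 | 0 |
| | adjusted | +0.30 | +0.20 | +0.10 |
| Partly transient, f = 1 − r | change score | −0.30 | −0.20 | −0.10 |
| | adjusted | 0 | 0 | 0 |
| Wholly transient, f = 1 | change score | −0.50 | −0.50 | −0.50 |
| | adjusted | −0.20 | −0.30 | −0.40 |

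Large simulations of these three settings agreed to within 0.01 SD. The two coefficients always differ by (1 − r)·d. Neither is unbiased for every f.

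For scale, with 33 people split 57:43, two-sided 5% and 80% power, the detectable difference is (1.96 + 0.84) × √(1/14.19 + 1/18.81) × √(2(1 − r)). This is 0.99 SD at r = 0.5 and 0.76 SD at r = 0.7.

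**3. Precision**

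Let ρ be the correlation between alcohol use and baseline. The variance of the alcohol coefficient with baseline adjustment, relative to the change score, is [(1 + r)/2] / (1 − ρ²):

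| | ρ = 0.2 | ρ = 0.4 |
|---|---|---|
| r = 0.5 | 0.75/0.96 = 0.78 | 0.75/0.84 = 0.89 |
| r = 0.7 | 0.85/0.96 = 0.89 | 0.85/0.84 = 1.01 |

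The gain runs from 22% lower variance to none. For a two-group gap with a 57:43 split, ρ² = 0.2451d²/(1 + 0.2451d²). A gap of 1.0 SD gives ρ² = 0.197, and at r = 0.8 the ratio is 0.90/0.803 = 1.12, so adjustment is then the less precise option.

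**4. The glucose entry window**

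Eligibility uses a finger-stick reading (Screening), while the analysed values come from separate OGTTs. A simulation with the Table 1 window of 94–124 mg/dL, an assumed SD of 12 mg/dL and group means of 95 or 100 gave a differential change of about 0 when the pre-intervention value was a separate measurement. When the screening reading itself served as baseline, and the group means differed, it gave ±1.0 to ±1.6 mg/dL.

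**The case against.** The strongest reply concerns the baseline value. The covariate list is illustrative and the article condenses a fuller document. A reader might infer that the plan excludes the baseline value; the text shows only that it is unnamed. That reply stands.

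A reader might also infer that the change-score model is biased towards the trial's hypothesis. That needs part of the gap to be transient. The article presents the alcohol difference largely as pathophysiology, in pancreatic response, mitochondrial function and gene expression, which suggests a substantial stable part. If the gap is stable, the change score is unbiased and baseline adjustment adds bias the other way (Lord's paradox). This also stands. It does not make the gap wholly stable: TLFB covers 30 days, PEth marks recent use, and the article itself allows that drinking may change during the study.

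Two further inferences fail. A sure loss of precision without baseline adjustment is not supported, as step 3 shows. Nor is a degrees-of-freedom cost from five age bands: the bands in Table 2 are descriptive, and no bands are specified for the regression.

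Finally, the regression is additional to the paired t-tests, and 33 is an interim count with enrolment expected to run to May 2023. Both limit the stakes. None of these replies rescues the balance sentence, which is a stated rule and not an omission.

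**Conclusion.** The balance rule is a firm but narrow defect: it rests on matching that is not described and a balance that is not defined, and it confuses coding with adjustment.

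The baseline point holds conditionally. Mean reversion is a real rival explanation for a larger improvement in at-risk drinkers, because the article reports both the worse starting values and the expectation. Under the assumed 0.5 SD gap, the spurious change-score coefficient lies between 0 and −0.50 SD depending on how much of the gap is transient. The adjusted coefficient lies between +0.30 and −0.40 SD for r of 0.4 to 0.8. The documents do not show where in these ranges the trial falls, so neither estimate should be taken as unbiased by default. The possible gain in precision is a secondary reason to show the adjusted estimate.

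The pre-post paired t-tests are untouched. The point affects only conclusions about alcohol use and response to exercise.

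**What to change.** - Delete the sentence on matching or balance.
- State that every alcohol regression includes age as a continuous variable and sex, whatever the observed balance.
- For each outcome, report the alcohol coefficient from the change-score model and from the model that adds the pre-intervention value of that outcome, side by side. Regressing the post value or the change on baseline gives the same alcohol coefficient, so either form will do.
- Next to them, state what each assumes: the change score is unbiased if the baseline gap is stable, and the adjusted estimate is unbiased if the transient share equals 1 − r. If the two disagree, describe the finding as dependent on that assumption.
- Use the pre-intervention OGTT value, not the screening finger-stick reading, as baseline for the glycaemic outcomes.

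The cost is a few lines of analysis text and one degree of freedom in the adjusted model. The baseline values are already collected for the pre-post comparison, and nothing changes in study conduct.
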